### Advanced multivariate statistical analyses

Finally, we will perform an exploratory analysis of the data using a multivariate data-driven approach. Analyzing separately behavioral data and several kinds of brain imaging data, cross-sectionally or over time, provides valuable information on these specific data. Additionally, combining diverse behavioral and different kinds of brain data within data-driven multivariate analyses may unravel hidden "covert" relationships [145, 146]. Specifically, we will perform multivariate data-driven analyses using multimodal Independent Component Analysis (ICA) [145, 146] and Partial Least of Squares (PLS) [147, 148] which have both been used successfully on multimodal brain imaging data.

Two methods will be used:

1) Joint, fusion, and linked ICA [149, 150] represent several blends of multimodal extensions of ICA that allow combining different types of data such as functional and structural neuroimaging data. The results of these analyses should reveal interactions between different types of information and consequently allow us to investigate differences between our groups / experimental conditions (interventions) [145, 149]. In addition, we will also decompose the fMRI data into functional brain networks using innovation-driven co-activation patterns (iCAPs), a recent approach of dynamic functional connectivity [151] that that can quantify temporal interactions between different networks.

2) PLS is another powerful technique that can identify components of multivariate relationships between imaging and behavioral data [148, 152], notably unified PLS correlation models [148]. This PLS technique allows revealing hidden relationships between all battery tests and MRI measurements over time and potentially show whether these relationships differ between the groups (machine-learning). We will also use PLS regression models to fit the best interventional neurobehavioral model for predicting the rehabilitation of elderly on a specific behavioral outcome i.e. evolution of the working memory performance. Implementations of these approaches are publicly available in addition to several in-house extensions that allow using them in the most flexible way, including machine-learning approaches [153, 154].

### Statistical power of the study

We performed a statistical power analysis for sample size estimation, based on the main outcome of this project, a significant group improvement at the COGTEL test. Data used for this analysis stem from a study on MCI patients by Biasutti et Mangiacotti (2018 [62], comparing musical instrumental practice (*n* = 15) to soft gymnastic activities (*n* = 14). In this study, the main outcome was a change over time in the MMSE score. Between baseline and the end of their twice weekly 3-month interventions, similar to the interventions in the current study, the MMSE performance did not change in the soft gymnastics group whereas it improved significantly in the musical instrumental practice group (F(1,33) = 13.906; *p* < 0.001; pη2 = 0.296). Such a partial η2 value corresponds to Cohen's effect size f of 0.65 which is considered large [155]. With an alpha = 0.05 and power = 0.80, projected sample size required for this effect size is *n* = 12 (GPower 3.1) [156].

The MMSE being highly correlated to the COGTEL (r = 0.93) [80], our proposed sample size of *n* = 16 per group (or *n* = 12 considering an attrition rate of 20%) seems reasonable for observing a significant COGTEL effect.

We recruit in two university hospital memory clinics; sample size was in the COVID context also determined according to their databases and recommendations, to ensure feasibility, but we will respect our power calculation above.

In general, it is difficult to recruit older adults for interventional neuroimaging studies. MRI measurements represent an impediment for older adults, even if they are mentally fit. Those studies therefore suffer from under recruitment. Even with fewer healthy older individuals than the number of patients suggested in the current protocol, many authors could still publish significant findings [157–163].

### Attrition / Drop-outs

A total of 16 volunteers will be recruited for each of the experimental patient groups and the control group. Thus, the intended total number of participants will be 48. Given the unclear future of the covid pandemic and the natural attrition in our patient population, our minimum aim is a total of at least 12 participants in each group at the completion of the six-month interventions and measurements, which corresponds to our power analyses (see section Statistical power of the study). We maintain the 16-person target for the control group. Thus, we predict a 20% attrition rate among the patients and will over-recruit 32 participants. We will not be able to compensate for dropouts because the interventions are ongoing.

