### Recruitment, practical details

The recruitment should have started for the first wave of patients in May 2020. Finally, the COVID-19 epidemic caused a 4–5 months delay in the original schedule, and we started recruitment in September 2020 lasting till November 2020.

Mainly because of the anxiogenic and restrictive context of COVID-19, but also for personal reasons (too much time involved, etc.), most patients that seemed to fulfil the criteria initially contacted by the MC-HUG finally chose not to participate. In the end, only 14 patients that met all criteria consented to participate, and of those 4 more interrupted their participation, 2 who went into early dementia, one quit for health reasons and a last individual for personal reasons. Ten patients followed the interventions and passed the measurements, which is not enough for valid analyses (see the section Statistical power of the study).

Therefore, we recruited a second wave of patients at the LMC-CHUV, participating in the study from November 2021 to July 2022 (prescreening, interventions, and all measurements), and a third wave participating between July 2022 and April 2023. We intend to recruit enough patients to bring the total to 16 for both experimental groups. Baseline measures (t0) for the second wave started in December 2021, and for the third wave from August 2022, after the inclusion process (pre-screening and first visit).

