### Before (t0, baseline), after 3 months (t1) and 6 months (t2) of interventions

#### A. Psychometric battery. Total duration: ~75 min. (interrupted by breaks)

D2-R test [88, 89]. Assesses attention, visual scanning accuracy and speed—8 min.Trail making Test A & B [90]. Visuo-motor task, assesses selective visual attention, processing speed and mental flexibility (Shifting)—5 min.Go-No-Go [91]. Inhibition task—5 min.Purdue Pegboard [94]. Evaluates visuo-manual skills and bimanual coordination—10 min.The Clock Drawing test [93] Evaluates apraxia and fine motor control and cognitive functions (visuo-construction, memory, spatial perception/representation, executive functions)—5 min.Laterality recognition test [96]. Assesses right/left judgements of body parts presented by photos on a tablet), evaluates the representation of the body schema- 10 min.Unipedal balance test [95] – < 5 min. Evaluates whole body balance.ERQ: Emotion Regulation Questionnaire [121]—10 min.WHOQOL-BREF [98]—5 min. Assesses well-beingCOGTEL [79, 80]. Provides a main (weighted) score of core cognitive function -10 min.

Nota bene: We will measure the COGTEL first during the prescreening (Supplementary Table 1, PRE-SCREENING STEP 3), then at t1 (3 months) and t2 (6 months) within the psychometric battery.

The Amsterdam Instrumental Activity of the Daily Living Questionnaire (Short Version; (A-IADL-Q(SV)) [97] – 25 min will be first filled in at prescreening, then sent by post at t1 and t2 (filled in with the caregiver, then verified in the laboratory).

A detailed list of the different psychometric measurements is provided in Supplementary Table 2.

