## Statistical analysis plan and sample size calculation

### Basic statistical analyses

First we will use linear mixed model equations (lme) using the open-source software R [144] to evaluate the longitudinal effects for all variables separately comparing both experimental groups to the control group and to each other. These lme are flexible and powerful statistical models that consider several levels of clustering, continuous, ordinal and categorical explanatory variables. They support unbalanced data and allow to integrate demographic data into the models. Our 2 patient groups may turn out unbalanced due to attrition. Moreover, because we are interested in development, we will incorporate the baseline scores in the models. This will allow correcting for differences between the groups at baseline.

We will also compare those results with more traditional multivariate analyses of covariance.

If the data are not normally distributed, and if data transformation cannot cope with this non-normality, we will either use robust analyses (weighting outliers or other influential observations) or use non-parametric approaches.

In testing multiple contrasts, adjustments of the alpha criterion for multiple comparisons will be applied.

Concerning the primary objective, the analysis will consist in evaluating increase or less decrease (experimental group 1 or 2 vs. the control group) of the total weighted score at the COGTEL test [79, 80] at t1 and t2 compared to baseline and to the passive control group, by means of lme and MANCOVA analyses, using a two-sided alpha criterion of 0.05.

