## Abbreviations

(f)MRI: (functional) Magnetic Resonance Imaging
A-IADL-Q(SV): The Amsterdam Instrumental Activity of the Daily Living Questionnaire (Short Version)
BBL: Brain and Behaviour Laboratory
CCER: Commission cantonale d’éthique de la recherche sur l'être humain de Genève
CER-VD: Commission cantonale d'éthique de la recherche sur l'être humain de Vaud
CHUV: Centre Hospitalier Universitaire Vaudois / Lausanne University Hospital
COGTEL: Cognitive Telephone Screening Instrument
COVID-19: Pandemic of the virus named SARS-CoV-2 (2019-nCoV)
CRIq: Cognitive Reserve Index questionnaire
DMN: Default Mode Network
DTI: Diffusion Tensor Imaging
EPI: Echo-Planar Imaging
ERQ: Emotion Regulation Questionnaire
FA: Fractional Anisotropy
FOV: Field Of View
GE: Geneva (Switzerland)
GEMMI lab: Geneva Musical Minds laboratory
Gold-MSI: The Goldsmiths Musical Sophistication Index
HADS: Hospital Anxiety and Depression Scale
HES-SO: Haute École Spécialisée de Suisse occidentale / University of Applied Sciences and Arts Western Switzerland
HEdS-GE: Haute école de santé de Genève HES-SO / Geneva School of Health Sciences
HUG: Hôpitaux Universitaires de Genève / Geneva University Hospitals
ICA: Independent Component Analysis
iCAPs: innovation-driven Co-Activation Patterns
lme: Linear mixed models equations
LMC-CHUV: Centre Leenaards de la Mémoire au Centre Hospitalier Universitaire Vaudois / Leenaards Memory Center at the Lausanne University Hospital
LREN: Laboratoire de recherche en neuroimagerie / Laboratory for Research in Neuroimaging
MANCOVA: Multivariate analysis of covariance
MC-HUG: Centre de la Mémoire des Hopitaux Universitaires de Genève / Memory Center of the Geneva University Hospitals
MCI: Mild Cognitive Impairment
MoCA: Montreal Cognitive Assessment
MP2RAGE: Magnetization-Prepared 2 Rapid Acquisition Gradient Echoes
MMSE: Mini-Mental State Examination
MRI: Magnetic Resonance Imaging
PCA: Principal Component Analysis
PLS: Partial Least of Squares
RCT: Randomized Control Trial
T: Tesla
t0: Baseline measurement
t1: 3-Month mid-term measurement
t2: 6-Month post-intervention measurement
WHOQOL-BREF: World Health Organization Quality of Life-BREF questionnaire (BREF for abbreviated)

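### Patients who stop training are given no route to a t1 or t2 COGTEL, so the primary analysis becomes a completer analysis with plausibly outcome-related loss; a 10-minute call could recover part of it

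*Protocol article*

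**What the plan says.** Four parts of the protocol article bear on this.

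- **Attrition / Drop-outs.** "A total of 16 volunteers will be recruited for each of the experimental patient groups and the control group". The stated minimum is 12 per group, counted at completion of both the six-month interventions and the measurements. Attrition of 20% is predicted among patients only, and the control target stays at 16. The section ends: "We will not be able to compensate for dropouts because the interventions are ongoing".
- **Withdrawal and discontinuation.** Patients may leave the study at any time, and a withdrawn patient's data are left out of the analyses. Where dementia is suspected, specialists and the principal investigator decide case by case whether training continues. A patient can therefore be off training without having withdrawn consent, but the section does not say whether that patient is still assessed.
- **A. Psychometric battery and Setting.** After prescreening, COGTEL is given at t1 and t2 within a battery of about 75 minutes, administered on site. Its entry reads: "Provides a main (weighted) score of core cognitive function -10 min". The Abbreviations list expands the name: "COGTEL: Cognitive Telephone Screening Instrument".
- **Recruitment, practical details.** In wave 1, 14 patients consented; "of those 4 more interrupted their participation, 2 who went into early dementia", one left for health reasons and one for personal reasons. The ten counted are those who both followed the training and were measured.

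The analysis sections plan linear mixed models (Basic statistical analyses) and imputation of missing data, for example by regularised iterative PCA (Data monitoring and quality assurance).

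**The concern.** The weighted COGTEL score is the primary outcome, and obtaining it requires neither the training nor the scanner. Yet the completion criterion, the place of COGTEL in the battery and the exclusion rule together tie its availability to staying in the programme. The patients lost this way are unlikely to resemble those who stay, since half of the wave 1 dropouts left with early dementia.

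The primary comparison sets patients against healthy controls, and attrition is predicted only among patients. Losing decliners from one side makes the patient arms look better. Neither the mixed model nor PCA imputation can recover a decline that was never measured, and the exclusion rule removes even the earlier scores that those methods would use.

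**Working it through.** **Inputs from the article.** 16 per arm, 32 patients, 16 controls; 20% predicted patient attrition; minimum 12 of 16; wave 1 loss 4 of 14; COGTEL 10 minutes; f = 0.65, alpha 0.05, power 0.80. **Assumption, not in the article:** the share r of dropouts who would give a COGTEL by telephone, which could be anything from 0 to 100%.

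**1. The plan's own figure.** Statistical power of the study: "Such a partial η2 value corresponds to Cohen's effect size f of 0.65 which is considered large". Check: f = √(0.296/0.704) = 0.648. A two-group F test at f = 0.65 and alpha 0.05 needs 11 per group (power 0.826), and 12 per group gives 0.861. The projected 12, used as completers per group, is reproduced to within one.

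**2. Expected loss.**
- Predicted: 0.20 × 32 = 6.4 patients, leaving 16 × 0.80 = 12.8 per arm.
- Stated minimum: 12/16 is a 25% loss, not 20%.
- Wave 1: 4/14 = 28.6% (exact 95% CI 8% to 58%). Applied to 32 patients this is 9.1, leaving 16 × 10/14 = 11.4 per arm.
- Chance that an arm of 16 keeps at least 12: 0.80 at 20% loss, 0.63 at 25%, 0.50 at 4/14.
- As a share of all 48 participants, with every control retained: 6.4/48 = 13% at 20% loss and 8/48 = 17% at 25%.

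**3. What calls could add.** Scores per arm at t2 are n = 16 × [1 − d(1 − r)] for loss d. The interval width is compared with that at r = 0, variance held constant: √(1/n + 1/16) against the controls, and √(1/n) for music versus psychomotor.

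| Loss d | n at r = 0 | n at r = 0.5 | n at r = 0.75 | Narrower vs controls | Narrower, music vs psychomotor |
|---|---|---|---|---|---|
| 20% | 12.8 | 14.4 | 15.2 | 3-4% | 6-8% |
| 25% | 12.0 | 14.0 | 15.0 | 4-6% | 7-11% |
| 4/14 | 11.4 | 13.7 | 14.9 | 5-7% | 9-12% |

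For example, √(1/12.8 + 1/16) = 0.375 and √(1/14.4 + 1/16) = 0.363, a ratio of 0.97. For the two patient arms, √(12.8/14.4) = 0.94.

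**4. Power is not assured to rise.** At f = 0.65, if recovered patients carry the full effect, going from r = 0 to r = 1 raises power from 0.883 to 0.945 (20% loss) or from 0.842 to 0.945 (4/14). If they carry no effect, power at r = 1 falls to 0.81 and 0.72.

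**5. Possible size of the bias (illustration only).** Suppose 2 in 14 patients convert and fall 1 to 1.5 SD further than the rest. Leaving them out overstates the mean patient change by 2/14 × (1 to 1.5) = 0.14 to 0.21 SD. The SD figures are assumed. The result applies to patients against controls and is the whole bias, not the part that calls would remove.

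**The case against.** **The sentence on not compensating for dropouts is about replacement.** This stands. It follows directly on the over-recruitment figure and says that lost patients cannot be made up for while training is running. A reader might infer that it writes off their outcomes, but it does not say so. The point rests on the completion criterion, the placement of COGTEL and the exclusion rule.

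**The article is condensed, and the full protocol may describe continued assessment.** The footnote to COGTEL is not shown and may state the mode of administration. That limits certainty. But the exclusion of withdrawn patients' data and the count of completers are stated rules, and they act in the same direction.

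**The patients who matter most may be the hardest to reach.** Three of the four wave 1 dropouts left for dementia or health, and patients may leave the study altogether. A reader might infer that a call would largely recover the missing scores. The documents give no recovery rate, so only partial recovery can be claimed.

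**The wave 1 rate is weak evidence.** The article does not say whether the four left before or after randomisation, and the interval is wide. The 20% prediction does not depend on it.

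**A mode flag cannot separate mode from dropout.** This stands: nearly all telephone scores would come from patients who stopped or missed visits. Omitting them in a sensitivity analysis largely returns to the completer set, so that analysis shows how much they matter but does not correct for mode.

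**Reach is limited.** Wave 1 ended in July 2021 and wave 2 was scheduled to July 2022, so gains computed on all 32 patients overstate what can still be achieved.

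**Conclusion.** The point holds as a worthwhile design improvement. The plan ties the primary outcome to completing the programme and does not separate stopping training from withdrawing consent. On its own figures, 20-29% of patients may lack a t2 COGTEL. A reader might take this as a fifth or more of all t2 scores; with controls retained, the 20% prediction is 13% of the 48 participants.

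The loss is plausibly outcome-related and would favour the patient arms against the healthy controls. A reader might also infer that the randomised music versus psychomotor contrast is biased. That requires such loss to differ by arm, which nothing in the article shows.

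The main gain from calling is less selection bias. Precision is secondary: intervals about 3-7% narrower against controls and 6-12% narrower for music versus psychomotor, assuming 50-75% recovery and unchanged variance. Power may rise or fall.

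**What to change.** For patients still to be followed:

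1. In Withdrawal and discontinuation and in Attrition / Drop-outs, separate stopping training from withdrawing consent to measurement.
2. Seek COGTEL in the t1 and t2 windows from every randomised patient who still consents, by telephone if a visit is not possible, and record the mode.
3. Analyse these scores, and all data collected before withdrawal where consent allows, under the randomised arm in the primary mixed model.
4. Reconcile the exclusion rule with the completion criterion and with the missing-data paragraph in Data monitoring and quality assurance. If the exclusion rule stays as it is, telephone scores from patients classed as withdrawn would be discarded.
5. Report a sensitivity analysis without telephone scores, stating that mode is largely confounded with dropout.

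The cost is about 10 minutes of existing staff time per call and one sentence in the consent form. Remote collection has a partial precedent in the trial: the daily-living questionnaire is already posted to patients at t1 and t2, then verified in the laboratory. The downside is a possible difference between telephone and in-person scores in a few patients.

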## Data monitoring and quality assurance

Data acquisition and quality is continuously monitored by the experimenters for each patient. A second quality check is performed on the server of the team where all data will be backed up (see Declarations**,** Availability of data and materials) and analyzed by the scientific collaborator (postdoc level) of the research team.

A third checkup is performed by an independent clinical Data Manager (scientific collaborator at PhD level) at the HEdS, who will regularly check all steps of the protocol as accepted by the ethical commissions (randomization, anonymization, inclusion/exclusion criteria, signed informed consent forms, questionnaires, data collection). All source data, documents and outcome data will be available to the monitor, without restriction.

The research team, including a Master student, will meet twice every month to discuss the progress of the study and encountered problems. Any urgent problem will be discussed immediately to assure the quality of the data collection (for instance sudden cognitive deterioration of a patient).

We will report reasons for the withdrawal of individuals for each randomization group and for the passive control group. Exact information on missing data at each time point will be reported in all publications. Missing data will be processed in the analyses with cutting edge means (for instance using the regularized iterative Principal Component Analysis (PCA) algorithm developed by Josse, Husson and Pagès (2009) [164], implemented in the R package missMDA).

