### Withdrawal and discontinuation

As mentioned in the informed consent form, patients can withdraw from the study at any time without providing a motivation.

If there is a suspicion of sudden cognitive impairment or the start of dementia, memory centers' professional medical doctors will validate or refute this suspicion. Whether patients may pursue interventions, if they so wish, will be determined on an individual basis by those specialists in agreement with the principal investigator of the study.

In the case of withdrawal, in the file containing the code and personal information of the patient, the date and motivation (or absence of motivation) will be mentioned, and the data of this patient will be excluded from the analyses.

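### Imputation is not confined to the analyses that need it, and the one method named would, if run once without arm, shrink the group effect

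*Protocol article*

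**What the plan says.** All statements are in the protocol article.

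- Data monitoring and quality assurance: "Missing data will be processed in the analyses with cutting edge means (for instance using the regularized iterative Principal Component Analysis (PCA) algorithm", as implemented in the R package missMDA. The section does not say whether one or several completed tables are produced, whether arm is used, or which analyses receive the result.
- Basic statistical analyses, first model: "First we will use linear mixed model equations (lme) using the open-source software R". The reason given for choosing it includes incomplete follow-up: "They support unbalanced data and allow to integrate demographic data into the models. Our 2 patient groups may turn out unbalanced due to attrition".
- Basic statistical analyses, second method: "We will also compare those results with more traditional multivariate analyses of covariance". The primary COGTEL score is analysed "by means of lme and MANCOVA analyses, using a two-sided alpha criterion of 0.05".
- Advanced multivariate statistical analyses: ICA and PLS on combined behavioural and imaging data.
- Withdrawal and discontinuation: when a patient withdraws, "the data of this patient will be excluded from the analyses".

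**The concern.** Regularised iterative PCA predicts each missing cell from the correlation structure of the whole table and shrinks the prediction. Without arm in the table, a missing 6-month score is predicted from the pooled pattern of all patients and carries little of that patient's arm effect. If such values are analysed as observed data, the contrast the trial exists to estimate is diluted.

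There are two routes into that contrast. The missing-data sentence covers the analyses in general, so nothing exempts the mixed model. MANCOVA, also named for the primary outcome, by default uses only complete rows and so invites a completed table. The mixed model gains nothing from this step, because a likelihood fit uses every observed visit and is valid under missing at random. With 16 patients per group and a stated minimum of 12, there is little precision to spare.

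**Working it through.** **1. The plan's own figures.** The article gives no figure for the effect of imputation; its figures set the scale of missingness. Partial η² = 0.296 gives f = √(0.296/0.704) = 0.648, matching the article: "Such a partial η2 value corresponds to Cohen's effect size f of 0.65 which is considered large". For a two-group one-way comparison at two-sided alpha 0.05, 12 per group has power 0.86, so the stated 12 is adequate if read as per group. Stated attrition is 20% (0.8 × 16 = 12.8 per group). Going from 16 to 12 is 4/16 = 25%. Missing rates of 5% to 25% were therefore examined.

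**2. Expected size, by hand.** Let a fraction m of 6-month scores be filled in, and let the filled-in values carry a share s of the true arm difference. The estimate is then about (1 − m(1 − s)) × the true effect. With s = 0 this is 95%, 90%, 80% and 75% of the truth at m = 5%, 10%, 20% and 25%. Attenuation should therefore be at most about equal to the missing fraction.

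**3. Simulation.** From the article: 16 per arm, three visits and COGTEL test–retest correlation 0.85. Assumed: 10 tests, between-test correlation 0.4, two PCA components, true effect 0.8 SD and 6-month visits missing completely at random. The analysis was a baseline-adjusted 6-month contrast between two arms, with 400 runs per setting. Ranges run over three cases: only COGTEL responds, the other tests respond half as much, all respond equally.

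| Missing at 6 months | PCA once, no arm: estimate ÷ truth | Coverage | Power | Observed data only: estimate ÷ truth | Power |
|---|---|---|---|---|---|
| 5% | 0.965–0.984 | 94–97% | 0.97–0.99 | 1.01–1.02 | 0.98–0.99 |
| 10% | 0.908–0.915 | 93–95% | 0.94–0.97 | 0.98–1.01 | 0.96–0.98 |
| 20% | 0.796–0.861 | 85–92% | 0.85–0.91 | 0.99–1.00 | 0.93–0.95 |
| 25% | 0.739–0.805 | 84–87% | 0.80–0.87 | 0.99–1.00 | 0.92–0.93 |

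The Monte Carlo error of a 95% coverage figure is √(0.95 × 0.05/400) = 1.1 points. The ratios agree with step 2.

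**4. Sensitivity at 20% missing.** Adding arm as one column still leaves the estimate 12–15% low, and five components leave it 17% low. With no true effect, the rejection rate after PCA is 5.2%, 3.8% and 4.0% at 10%, 20% and 25% missing, so type I error is not inflated.

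**5. Other simulations, true effect 0.50 SD.**
- 3,000 runs, 9 tests: 0.45 at 10% missing and 0.38 at 25%, against 0.51 on observed data.
- A separate set, 16 per arm: about 0.48, 0.45, 0.40 and 0.375 at 5%, 10%, 20% and 25%, against 0.48–0.50 on observed data. The pull toward zero also appeared when one group started 1 SD lower, as the patient groups might against healthy controls.
- 600 runs, 13 or 16 per arm: 0.465–0.49 at 5% and 0.44–0.47 at 10%, with coverage 93–96%.

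**6. Where the lost coverage comes from.** In the 3,000-run set at 25% missing, the mean is 0.381, the empirical standard error 0.187 and the model standard error 0.182. With 29 degrees of freedom the half-width is 2.045 × 0.182 = 0.372.
- Coverage of 0.50: Φ((0.872 − 0.381)/0.187) − Φ((0.128 − 0.381)/0.187) ≈ 0.91.
- Without bias: 2Φ(0.372/0.187) − 1 ≈ 0.95.

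The shortfall is therefore bias; the two standard errors differ by only 3%.

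**7. Which missingness reaches the imputation.** Withdrawn patients are excluded, so the predicted 20% attrition would mostly not be imputed. What remains are gaps in patients who stay. The article does not predict their rate, so the 5–10% rows are the more relevant ones and the 20–25% rows an upper bound.

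**The case against.** The strongest reply is that the article does not commit to the harmful version. PCA is introduced as an example. The text does not say that it is run once, that arm is left out, or that the mixed model runs on completed data. The mixed model comes first and is already presented as the answer to attrition, while MANCOVA, ICA and PLS give imputation a legitimate use. Much of this detail normally sits in an analysis plan that is not shown.

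This stands as far as it goes: the harm is conditional. It does not dispose of the point, because the document names one tool, applies it to the analyses without limit, and names MANCOVA as well as the mixed model for the primary outcome.

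Three stronger readings are tempting and not supported:
- A reader might infer that the plan ignores arm and will shrink the effect. The text does not say so.
- A reader might apply the 20–25% results to the predicted attrition. The exclusion of withdrawn patients prevents that.
- A reader might infer that intervals are too narrow because filled-in values carry no noise. The standard errors in step 6 do not show this.

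Two further limits stand. The simulations used a baseline-adjusted contrast in place of the full mixed model. The contrast with the non-randomised healthy controls was examined only through the case of a 1 SD lower start.

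**Conclusion.** The point holds in conditional form. If the named method is run once without arm and its output enters the group contrast, the effect is attenuated by roughly 2–5% at 5% missing 6-month visits, about 10% at 10%, and 14–26% at 20–25%, the last as an upper bound. The simulations agree on direction and broadly on size, and the hand calculation explains why. The figures rest on assumed effect sizes, test correlations and numbers of components, and on data missing at random or completely at random.

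The planned mixed model avoids the problem without imputation, so restricting where imputation applies is a better choice at almost no cost. A related inconsistency belongs with it: the article chooses mixed models partly because they accommodate attrition, then excludes the data of patients who withdraw, which discards the observed visits those models would use.

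**What to change.** - In Data monitoring and quality assurance, state that the primary and secondary mixed-model analyses are fitted to all observed visits with no imputation.
- Confine imputation to analyses that need a complete table (MANCOVA, ICA and PLS). Use multiple imputation that accounts for arm there, in place of a single PCA fill-in. Adding arm as one column to a single fill-in is not enough (step 4). Separate PCA within each arm of 12–16 patients is untested and should not be required.
- Reconcile the exclusion of withdrawn patients' data in Withdrawal and discontinuation with the reliance on mixed models for attrition in Basic statistical analyses.

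The cost is a few sentences and a little more analysis work. No change to data collection or sample size is needed.
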